### Withdrawal

Withdrawal criteria include a sustained compliance of less than 80%, hyperkalemia despite reduction of dosage or intolerable side effects.

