## Methods

One hundred seventy kidney transplant patients will be included from four Danish hospitals covering all Danish renal transplant centers (Odense, Copenhagen and Aarhus). Patients are recruited from outpatient clinics in the Departments of Nephrology at Odense University Hospital, Kolding Hospital, Rigshospitalet, Copenhagen and Aarhus University Hospital, respectively. Eligibility criteria are listed in Table 1.

**Table 1 Tab1:** Eligibility criteria

Inclusion criteria	Exclusion criteria
Age > 18 years	Former intolerance of spironolactone
Tacrolimus/cyclosporine treatment	Potassium binder or digoxin treatment
Proteinuria < 3 g/day	Pregnancy or planned pregnancy
Creatinine clearance ≥30 mL/min	Clinically relevant organic, systemic or psychological disorder
Plasma potassium < 5.5 mmol/L	Expectation of non-compliance
Negative pregnancy test at inclusion for women of childbearing potential and adequate contraception throughout the trial	

Wide eligibility criteria have been chosen to obtain a high generalizability of the results. This study includes renal transplant patients with a stable kidney function at the time of inclusion. Even in stable patients, a gradual deterioration of renal function is expected. Previous studies have found an average rate of decline of glomerular filtration rate in of 1–3 mL/min/year [23–26]. Hence, we chose a follow up of 3 years.

Patients are randomized 1:1 to spironolactone (Spirix®) or placebo for three years. Initial dosage is 25 mg once daily, which is doubled after three months, if tolerated well. At inclusion and yearly hereafter a standard workup is performed including chrome-EDTA clearance, 24-h urine collection, electrocardiogram, 24-h ambulatory blood pressure measurement and blood- and urine samples (Fig. 1). Anonymized samples are stored at − 80 °C until analyses. In a subgroup (*n* = 50) graft biopsies will be performed at inclusion and after two years. All registrered variables are listed in Table 2.

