### Outcome

Outcomes are summarized in Table 3.

**Table 3 Tab3:** Study outcomes

Primary endpoint	Secondary endpoints
Chrome-EDTA clearance	24 h urinary protein excretion
	Renal fibrosis (morphology)
	Cardiovascular events
	Biomarkers of fibrosis in tissue, blood and urine

The primary endpoint is renal function evaluated by chrome-EDTA clearance, in which glomerular filtration rate is calculated from the area under the plasma clearance curve after a single intravenous doses of ^51^CrEDTA. Plasma concentrations of ^51^CrEDTA can be determined with a single blood sample by measuring residual radioactivity 4 h after the injection or by multiple samples 4, 5 and 6 h after the injection. For centers using a single blood sample after 4 h, an additional blood sample is performed 24 h after the injection in male patients with plasma creatinine ≥200 μmol/L and female patients with plasma creatinine ≥150 μmol/L. In repeat chrome-EDTA clearance measurements the coefficient of variation is 8–10% [27].

Secondary endpoints include 24-h urinary protein excretion, cardiovascular events (death, myocardial infarction, stroke or peripheral arterial thrombosis) and renal fibrosis. For the latter, Masson Trichrome stained sections of kidney allograft biopsies will be used for measuring Banff chronicity scores and calculating morphologic fibrosis by point counting. Point counting provides a quantitative and reproducible estimation of the extent of fibrosis [28]. In brief, the software systematically selects sections of renal cortex and superimposes a grid on a computerized image. The extent of fibrosis is determined by counting the fraction of intersection points that overlie fibrotic areas relative to normal tissue. Limitations of both Banff scoring and point counting are the risk of sampling error as well as the somewhat subjective evaluation of fibrosis. In this study all biopsies will be reviewed by the same pathologist to avoid inter-observer variability.

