### Safety

Plasma potassium and -creatinine levels are monitored closely at initiation of therapy and after any dose adjustment. Sustained potassium levels > 5.8 mmol/L will result in reduction of dosage to 25 mg per day. In case of hyperkalemia on 25 mg per day, the patient will be withdrawn from the study. Potassium binding resins will only be used to handle cases of acute hyperkalemia, thus chronic treatment with resins is not allowed. Hyperkalemia is registered as an adverse event in case of an absolute increase of > 1.5 mmol/L or any increase to a level above 5.5 mmol/L. All significant increases in plasma creatinine are evaluated by study investigators, and in case of doubt of the etiology, the study drug is discontinued until renal function has stabilized. All adverse events registered throughout participation in the study will be recorded. Serious adverse events are defined according to Good Clinical Practice as events that result in death, are life threatening, require hospitalization, cause prolongation of existing hospitalization or result in persistent or significant disability/incapacity. The project safety board continuously monitors serious adverse events to identify general study safety issues.

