### Allocation and blinding

After completing the baseline workup (Fig. 1), patients are allocated to consecutive randomization numbers. Randomization has been performed by the pharmacy at Odense University Hospital in blocks of four. The allocation code is blinded to both patients and investigators and is solely known by the pharmacy. Opaque envelopes containing the individual allocation are available on site in case of the need for emergency unblinding. If the allocation code is revealed before completing the trial the patient will be excluded.

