### Statistical methods

All statistical analyses will be done using STATA software. All generated variables will be documented by do-files. The main analysis will be performed as intention-to-treat using last-observation-carried-forward. Sub-analyses will include per protocol analyses and “best case”/“worst case” analyses. Where appropriate, variables will be analyzed using parametric or non-parametric tests.

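### Withdrawing patients from the study, rather than only from the drug, replaces their 3-year GFR with a carried-forward value in an analysis declared as intention-to-treat

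*Protocol article*

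**What the plan says.** All references are to the protocol article.

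- **Withdrawal** lists three grounds together: "Withdrawal criteria include a sustained compliance of less than 80%, hyperkalemia despite reduction of dosage or intolerable side effects".
- **Safety** gives the consequence for one of them: "In case of hyperkalemia on 25 mg per day, the patient will be withdrawn from the study".
- **Safety** words an interruption of the drug alone differently. It does so for creatinine rises of unclear cause: "in case of doubt of the etiology, the study drug is discontinued until renal function has stabilized".
- **Outcome** fixes the endpoint: "The primary endpoint is renal function evaluated by chrome-EDTA clearance".
- **Methods** fixes the measurement times and duration: "At inclusion and yearly hereafter a standard workup is performed including chrome-EDTA clearance" and "Hence, we chose a follow up of 3 years".
- **Statistical methods** fixes the main analysis: "The main analysis will be performed as intention-to-treat using last-observation-carried-forward". It also plans per-protocol and best-case/worst-case sub-analyses.

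No section provides for chrome-EDTA clearance to be measured after a patient has been withdrawn.

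**The concern.** An intention-to-treat comparison needs each randomised patient's outcome whether or not the drug was tolerated or taken. Here, intolerance and poor adherence are themselves the grounds for withdrawal. Where withdrawal means leaving the study, the protocol's own rule creates the missing 3-year values, and LOCF then fills them.

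Two features make this more than a formality. First, hyperkalemia is described in the Discussion as a recognised risk of mineralocorticoid receptor antagonists, and side effects are also plausibly drug-related, so the loss may differ between arms. Second, GFR is expected to fall over time, so an earlier value is on average too high as a stand-in for year 3. If one arm loses more patients, or loses them earlier, the between-arm difference is distorted. No analysis plan can repair this later, because the values were never measured.

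**Working it through.** **Inputs from the article.** Expected decline b = 1–3 mL/min/year; chrome-EDTA clearance at years 0, 1, 2 and 3 (both Methods). SD 10 mL/min, target difference 5 mL/min, power 80%, significance level 0.05, 63 per group, 15% dropout, 170 in total (Sample size). 1:1 allocation (Methods), so 85 per arm.

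**Reproducing the plan's figure.** n per arm = 2 × (1.96 + 0.8416)² × 10² / 5² = 62.8, rounded up to 63, or 126 in total. This matches a two-sided test.

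**Step 1: decline omitted per withdrawn patient.** Omitted decline = b × (3 − year of last value).

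- Baseline value only: (1 to 3) × 3 = 3–9 mL/min.
- Last value at year 1: (1 to 3) × 2 = 2–6 mL/min.
- Last value at year 2: (1 to 3) × 1 = 1–3 mL/min.

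The baseline-only case is realistic. Treatment starts at 25 mg, so hyperkalemia on that dose can occur well before the first yearly measurement.

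**Step 2: bias in the between-arm difference.** Assume no treatment effect, equal decline in both arms and the same timing of withdrawal. Then bias = (proportion withdrawn on spironolactone − proportion withdrawn on placebo) × omitted decline. The article gives no withdrawals by arm, so every split below is an assumption. A positive value favours spironolactone.

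| Assumed split | Baseline value only | Last value at year 1 | Last value at year 2 |
|---|---|---|---|
| 15% vs 15% | 0 | 0 | 0 |
| 20% vs 10% | 0.3–0.9 | 0.2–0.6 | 0.1–0.3 |
| 20% vs 5% | 0.45–1.35 | 0.3–0.9 | 0.15–0.45 |
| 25% vs 5% | 0.6–1.8 | 0.4–1.2 | 0.2–0.6 |

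For the 20% vs 5% row: 0.15 × 3 = 0.45 and 0.15 × 9 = 1.35; 0.15 × 2 = 0.3 and 0.15 × 6 = 0.9. This row averages 12.5% withdrawn; the others average the stated 15%.

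**Step 3: effect on the test.** SE = 10 × √(2/85) = 1.53 mL/min, assuming that carrying values forward leaves the SD at 10. The two-sided type I error is 1 − Φ(1.96 − bias/SE) + Φ(−1.96 − bias/SE). For 20% vs 5% it rises from 5% to about 6–14% (baseline value only) or about 5–9% (last value at year 1).

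**Step 4: direction.** The Discussion notes that creatinine tends to rise when these drugs are started and that the rise reverses on stopping. If measured GFR fell on drug by h in the same way, and an on-drug value were carried forward, the net error per patient would be omitted decline − h. It changes sign once h exceeds the omitted decline (2–6 mL/min for a year-1 value). The article gives no figure for h. A carried-forward baseline value precedes treatment and is not affected.

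**The case against.** **The article is condensed, and the full protocol may continue follow-up.** This carries some weight for low compliance and side effects, where the article does not say what the patient is withdrawn from. It carries less for hyperkalemia, where departure from the study is stated outright and stopping the drug alone is worded differently in the same section.

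**Withdrawn patients are not excluded.** This stands. A reader might infer that the main analysis becomes a comparison of patients who tolerate the drug with adherent placebo patients. It does not: LOCF keeps every withdrawn patient in. The defect is an out-of-date value, not a missing patient.

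**The best-case/worst-case sub-analyses already cover this.** They show how far the missing values could matter, but they do not recover them and they are not the main analysis.

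**The loss may be balanced.** This also stands as a possibility. It is tempting to say that most losses come from the spironolactone arm, but no section gives withdrawals by arm and the compliance criterion is not specific to either. In the 8-week eplerenone safety study cited in the Discussion, none of 31 patients was withdrawn for hyperkalemia.

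**Other stronger readings that the article does not support.**

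- That any hyperkalemia, missed tablet or side effect ends participation. Safety provides for dose reduction to 25 mg first, low compliance must be sustained, and side effects must be intolerable.
- That 126 of 170 implies 26% (44 patients) without a year-3 value. The stated dropout is 15%, and 126/0.85 gives 149. That 170 exceeds this is a separate sample-size question.
- That power falls from about 90% (85 per arm) to 80% (63 per arm). LOCF analyses all 170, and 80% is the designed power.
- That later deaths and cardiovascular events are certainly lost. The article does not say what happens to event follow-up after withdrawal.

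**Conclusion.** The concern holds in a limited form. The study-exit rule in Safety, explicit for hyperkalemia on 25 mg and implied for the other two criteria, does not fit the intention-to-treat principle in Statistical methods. A patient handled under it has a 3-year GFR that is carried forward rather than observed.

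Per withdrawn patient the omitted decline is comparable to the 5 mL/min target. Across the trial the bias is smaller. At 20% vs 5% it is at most 1.35 mL/min, or 27% of the target (1.35/5). It is zero if withdrawal is equal in number and timing, and it could reverse if a drug-related fall in GFR were carried forward. Size and direction rest on an assumed split, assumed timing, equal decline and no treatment effect; only the decline rate comes from the article. The conflict between the sections is clear for hyperkalemia, while the size of its effect is not established. This is a cheap improvement, not a demonstrated failure of the trial.

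**What to change.** Reconcile Safety, Withdrawal and Statistical methods by separating two events, stopping study drug and leaving follow-up:

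1. State that meeting a withdrawal criterion ends study drug, not participation.
2. Keep the 1-, 2- and 3-year chrome-EDTA clearance, 24-h urine collection and event follow-up for all randomised patients unless they withdraw consent.
3. Include values measured off drug in the main intention-to-treat analysis.
4. Use the 80% compliance limit only to define the per-protocol set.

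This leaves unchanged when study drug is reduced or stopped.

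**Cost.** A short amendment and a letter to sites. The yearly visits are already in the schedule, but keeping patients who are off drug in follow-up takes some effort. Off-drug values dilute the estimated effect, which is what an intention-to-treat estimate is meant to reflect. Visits already missed by withdrawn patients cannot be restored: inclusion began in January 2013. Trial status reports 142 active patients in November 2017 with inclusion still open, so much of the three-year follow-up could still benefit.

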### Sample size

Assuming a standard deviation in chrome-EDTA clearance of 10 mL/min, a sample size of 126 patients (63 in each group) will be able to detect a difference in chrome-EDTA clearance of 5 mL/min between the groups with 80% power and a significance level of 0.05. With an expected dropout rate of 15%, the planned total was set to 170 patients.

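### The SD of 10 mL/min behind the sample size has no stated scale or source, and no baseline-adjusted analysis of chrome-EDTA clearance is named to go with it

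*Protocol article*

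**What the plan says.** The Sample size section of the protocol article begins "Assuming a standard deviation in chrome-EDTA clearance of 10 mL/min" and aims to "detect a difference in chrome-EDTA clearance of 5 mL/min between the groups" "with 80% power and a significance level of 0.05". This gives 126 evaluable patients, 63 per group. The planned total of 170 is attributed to an expected 15% dropout. No source is given for the SD.

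The Outcome section and Table 3 name chrome-EDTA clearance as the primary endpoint, without reference to change or slope. Under Statistical methods the main analysis is intention-to-treat with last observation carried forward, and the choice of test is left open: "Where appropriate, variables will be analyzed using parametric or non-parametric tests". No baseline adjustment is mentioned.

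Under Methods, clearance is measured at inclusion and yearly. On eligibility the text says "Wide eligibility criteria have been chosen to obtain a high generalizability of the results". Table 1 sets a floor of 30 mL/min for creatinine clearance and no upper limit. The Outcome section gives a coefficient of variation of 8–10% for repeat clearance measurements. It also shows that sampling differs by centre, with an extra rule "For centers using a single blood sample after 4 h" and a three-sample scheme as the alternative.

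**The concern.** A power calculation is informative only if its SD belongs to the quantity that will be compared. Here the SD, the target difference and the endpoint are all worded as clearance itself, and the stated tests suggest a direct comparison of two groups. On that wording, 10 mL/min has to cover every source of spread between patients: true differences in graft function across a deliberately broad population, measurement error, and any difference between the centres' sampling schemes.

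If the spread of raw clearance is wider than that, a direct comparison has less power than stated. This matters because the article justifies the trial as the sufficiently powered study that earlier ones were not. If instead 10 describes change or a residual after baseline adjustment, the figure may be sound, but the article names no analysis on that scale.

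**Working it through.** **Inputs from the article.** Difference 5 mL/min; SD 10 mL/min; alpha 0.05 (sidedness not stated); power 80%; 1:1 allocation; 170 planned; 15% dropout; CV 8–10%.

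**Inputs assumed.** Raw SD of 12, 15 or 20 mL/min; baseline-to-year-3 correlation r; mean clearance of 50 mL/min for the measurement-error check. The article gives none of these.

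**1. Reproduce the stated size.** n per group = 2(1.96 + 0.8416)² × 10² / 5² = 62.8, rounded up to 63, or 126 in total. This matches the article. It is a two-sided, unadjusted comparison of two means; a one-sided test would need 50 per group.

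**2. Slack in the total.** 126 / 0.85 = 148.2, so 149 patients would cover 15% dropout. The plan has 170. With 15% dropout, 170 × 0.85 = 144.5, or about 72 per arm.

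**3. Unadjusted power for 5 mL/min if the raw SD exceeds 10** (two-sided t-test):

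| SD (mL/min) | 63 per arm | 72 per arm | 85 per arm (all 170) |
|---|---|---|---|
| 10 (stated) | 80% | 85% | 90% |
| 12 (assumed) | 64% | 70% | 77% |
| 15 (assumed) | 46% | 51% | 58% |
| 20 (assumed) | 29% | 32% | 37% |

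The slack softens the loss at SD 12 but does not bring any of the assumed larger SDs up to 80%.

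**4. Could 10 be a raw SD?** At an assumed mean of 50 mL/min, the CV gives a measurement SD of 4–5. A total of 10 then leaves √(100 − 16) = 9.2 to √(100 − 25) = 8.7 for true differences between patients. For scale only, an even spread of width w has SD w/√12: 30–65 mL/min gives 10.1 and 30–90 gives 17.3. This makes a raw SD above 10 plausible. It does not measure it.

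**5. Could 10 be an SD of change?** Two measurements with error SD 4–5 give a change SD from error alone of 4√2 = 5.7 to 5√2 = 7.1. A total of 10 leaves √(100 − 32) = 8.2 to √(100 − 50) = 7.1 for true variation in change. That is credible.

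**6. What baseline adjustment would give.** Residual SD = SD × √(1 − r²). For a residual SD of 10, r = √(1 − (10/SD)²): 0.55 at SD 12, 0.75 at SD 15, 0.87 at SD 20. Power at 72 per arm:

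| Raw SD (assumed) | r = 0.7 | r = 0.8 | r = 0.9 |
|---|---|---|---|
| 15 | 79% | 91% | above 99% |
| 20 | 55% | 70% | 93% |

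Every entry exceeds the unadjusted figure (51% and 32%), but not every entry reaches 80%.

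**The case against.** The strongest reply is that 10 mL/min was meant as a within-patient quantity. The article justifies three years of follow-up by an expected decline of 1–3 mL/min/year, or 3–9 mL/min in total, so a target of 5 mL/min reads naturally as a difference in change. The Trial status section says the interim analysis compared rates of decline. Step 5 shows that 10 is credible for change. This stands, and on that reading the sample size has no shortfall. It does not remove the point, because the endpoint, the SD and the tests are not worded on that scale.

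A reader might go further and infer that raw clearance certainly varies by more than 10 mL/min and that 80% power is therefore not delivered. The documents do not support that. They give no between-patient SD, no mean clearance and no baseline correlation, so the lower power figures hold only under the assumed SDs.

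A reader might also infer that the trial decided not to use baseline clearance. The article is silent. It excludes no covariate, a parametric test could include ANCOVA, and an analysis plan that is not shown may settle the model. That defence covers the choice of covariates. It does not cover the scale of the SD, because the sample-size basis is stated in this article.

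**Conclusion.** The point holds in conditional form. Either 10 mL/min is a raw SD, unsourced and plausibly too small for the population described, or it is a change or residual SD that the stated endpoint and tests do not match. The text needs correcting in both cases.

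In the first case, unadjusted power at 72 per arm is about 70%, 51% or 32% for assumed raw SDs of 12, 15 or 20 mL/min, and even with all 170 analysed it is 77%, 58% or 37%. In the second case the stated power stands, provided the analysis is run on that scale.

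It would also be too strong to say that adjustment restores 80% power. That depends on a correlation the article does not give: about 0.75 or more at raw SD 15 and 0.87 or more at raw SD 20 to reach a residual SD of 10. I rate the point as moderate, with medium confidence.

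**What to change.** Name one primary analysis: the between-arm difference in chrome-EDTA clearance at year 3, adjusted for baseline clearance, by ANCOVA or the equivalent repeated-measures model. This replaces the open choice between parametric and non-parametric tests for the primary endpoint. Centre is a reasonable optional covariate because sampling schemes differ between centres, although the article gives no size for any such difference.

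In the Sample size section, say which scale the SD of 10 mL/min refers to and where it comes from. If it is not the residual SD, restate the power for the adjusted analysis with the raw SD and the correlation made explicit. Both could be estimated from pooled, blinded clearance data.

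The cost is a few sentences and one covariate, or two with centre. Clearance is already measured at inclusion, so no new data are needed, and adjustment also removes the effect of chance baseline imbalance.

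### The dropout step of the sample size is wrong: 126 evaluable patients with 15% dropout need about 149 to 150 enrolled, not 170 (a conservative error)

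*Protocol article*

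**What the plan says.** The Sample size section of the protocol article gives its inputs in full: an SD of 10 mL/min, power of 80% and a 5% significance level. From these it concludes that "a sample size of 126 patients (63 in each group) will be able to detect a difference in chrome-EDTA clearance of 5 mL/min". A separate sentence then moves from evaluable to enrolled patients: "With an expected dropout rate of 15%, the planned total was set to 170 patients".

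The Methods section repeats the total ("One hundred seventy kidney transplant patients will be included from four Danish hospitals") and gives the allocation ratio as 1:1. The abstract also gives 170. The article mentions no second power target, rounding margin or further allowance that would link 126 and 15% to 170.

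**The concern.** The sentence offers 15% dropout as the only reason for going from 126 to 170. Inflating 126 by 15% in either usual way falls well short of 170, so the input and the result in that sentence do not belong to one calculation.

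What is at stake is whether the enrolment target can be traced. About 20 more patients than the stated inputs require are to be enrolled into three years of study treatment with yearly clearance measurements, and a reader should be able to see why. The article also describes the trial as sufficiently powered, yet gives no power figure that matches the number it plans to enrol.

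**Working it through.** **Inputs (Sample size section; allocation from Methods).** Difference 5 mL/min; SD 10 mL/min; power 80%; significance level 0.05; 1:1 allocation; dropout 15%; planned total 170. Sidedness is not stated. Two-sided is assumed because it reproduces the plan's figure, whereas a one-sided test gives 50 per arm, 100 in total.

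**Step 1: reproduce the 126.**
n per arm = 2 × (1.960 + 0.842)² × (10/5)² = 62.8, rounded up to 63, so 126 in total. This agrees with the plan. The exact t-test gives 63.8, so 64 per arm and 128 in total, which is close enough to raise no issue.

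**Step 2: add the dropout allowance.**

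| Evaluable patients | N / (1 − 0.15) | N × 1.15 |
|---|---|---|
| 126 (plan) | 148.2 → 149 (150 with equal arms) | 144.9 → 145 |
| 128 (t-test) | 150.6 → 151 (152 with equal arms) | 147.2 → 148 |

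The first column is the correct inflation; the second is the common short-cut. Neither gives 170. Against the correct figure for the plan's own 126, the excess is 170 − 149 = 21 patients (14%), or 170 − 150 = 20 (13%) with equal arms. That is too much for rounding.

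**Step 3: what 170 with 15% dropout provides.**
170 × 0.85 = 144.5, so about 144 evaluable, 72 per arm.
Standard error of the difference = 10 × √(2/72) = 1.667 mL/min.
5 / 1.667 = 3.00, and 3.00 − 1.96 = 1.04, so power = Φ(1.04) ≈ 85.1%. The t-test gives 84.6%.

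**Step 4: could a different target explain 170?**
At 85% power the formula gives 72 per arm, 144 in total, and 144 / 0.85 = 169.4, which rounds up to 170. At 90% power with no dropout it gives 85 per arm, exactly 170. Either could be the origin of the number, but the article states neither, so this is conjecture.

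**The case against.** The strongest defence is that nothing the section says about power is false. The 80% is attached to 126 evaluable patients, and 170 enrolled with 15% lost leaves more than 126. The wording presents 170 as a chosen number, which could cover a deliberate margin, and a condensed article may omit the reason. Power and enrolment are, if anything, better than the stated inputs require.

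Most of this stands. The 126 is right, the 80% is correctly attached to it, and the error is conservative. What does not stand is the appeal to an unstated margin. The sentence gives one reason for 170, and that reason yields 149 to 150. A margin of about 20 patients is nearly as large as the correct dropout allowance itself (149 − 126 = 23). This is a stated input and a stated result that disagree, not a detail left to a fuller document.

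Two stronger readings are tempting, and the documents do not support them:

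- A reader might infer that the trial really plans for 26% dropout, since 1 − 126/170 = 25.9%. The article says 15%; the 26% appears nowhere and is only a back-calculation. The plan is not ambiguous between the two rates.
- A reader might infer that a dropout allowance conflicts with the intention-to-treat analysis by last observation carried forward in the Statistical methods section. It does not. Patients with carried-forward values contribute less information about the three-year difference, and per-protocol analyses are also planned, so an allowance for losses is reasonable.

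**Conclusion.** The point holds for the dropout step only. On the stated inputs the enrolled total should be about 149 to 150, and 170 does not follow by either usual inflation. If 170 and 15% are both kept, the trial has about 144 evaluable patients and about 85% power, against the 80% quoted for 126. This rests on a two-sided test, on a two-group comparison of means with the plan's SD and difference, and on dropouts being treated as lost to the analysis, as the plan's own allowance implies.

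Severity is minor. The discrepancy favours power, leaves the analysis untouched and introduces no bias. It would be wrong to conclude that the trial is underpowered or that the whole sample size calculation fails.

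**What to change.** Keep 170 and replace the final sentence of the Sample size section with one consistent statement. Suggested wording: a total of 170 patients, with 15% dropout, leaves about 144 evaluable and gives about 85% power for a 5 mL/min difference at SD 10 mL/min. If 170 was in fact set with a specific margin or another dropout rate, state that instead.

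The dropout assumption should not be refitted to about 26% merely to make the arithmetic close. The Trial status section reports 142 active patients by November 2017, so a rate chosen now to match the total would be retrospective.

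The cost is one sentence, with no change to enrolment, conduct or analysis.
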